### Record retention and confidentiality

Participants who proceed to the trial assessment will receive a trial code. Organizers will record and store all data collected in the study in an electronic database on a secure server build. All databases will be anonymized—all identifiers will be irreversibly removed, and subjects will no longer be identifiable. All principal investigators will have access to a secured database.

### Withdrawal from the trial

Participants may voluntarily withdraw from the trial for any reason at any moment.

### Sample size calculation

The sample size was determined in relation to the between-group effect size and calculated using G*Power software. Previous research on an online UP intervention and online interventions for AjD has revealed a between-group effect size at the level of *d* = 0.5 and a within-group effect size at the level of *d* = 0.63 [42, 87]. Assuming an alpha 0.05 with a power of 0.80 and post-treatment between-group effect size of *d* = 0.5 (iCBT-UP versus control), 190 participants in the three groups will be sufficient to detect assumed differences. However, because the literature reveals dropout rates from online CBT interventions, with minimal guidance, of approximately 30% [88], a total sample of 247 participants will be recruited.

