#### Internet progressive muscle relaxation training (iPMR)

Training in the comparison condition is based on PMR principles [53]. Studies have shown that relaxation reduces stress, anxiety, and depression among university students [54]. One of the most often used researched relaxation techniques is PMR [55]. PMR has been proven to reduce college students’ anxiety and stress and boost happiness [56, 57]. In the present study, we want to evaluate whether changes obtained in iCBT-UP will be significantly higher, than those obtained in an active, well-researched comparator. The PMR training aims to teach how to quickly achieve a state of relaxation. It is also a modular intervention. It consists of five modules (the first module lasts 2 weeks). See Table 2. Participants are asked to practise techniques from each module twice a day. The intervention is also interactive and contains videos introducing new topics to participants and audio-guided relaxations.

**Table 2 Tab2:** Overview of iPMR intervention

Number	Name	Description
Module 1	Progressive Muscle Relaxation of 16 Group of Muscles	Participants learn how to tighten and relax 16 groups of muscles. This module is recommended to last for 2 weeks
Module 2	7 Muscle Group Relaxation	This is a shortened version of PMR. Participants learn how to tighten and relax 7 groups of muscles (first arm, second arm, head, neck, torso, first leg, second leg)
Module 3	4 Muscle Group Relaxation	This is a shortened version of PMR. Participants learn how to tighten and relax 4 groups of muscles (arms, head, torso, legs)
Module 4	Release Only Condition	Module in which participants are taught to obtain a state of relaxation without tightening muscles
Module 5	Your Own Experience	In this module, participants are engaged to train relaxation on their own—without audio recordings. They can do so in different situations in their daily lives and in different body positions

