## Discussion

To our knowledge, there is no published study evaluating the effectiveness of an online psychological intervention for students experiencing AjD. Our study is meant to fill this gap. The study aims to examine the effectiveness of an internet psychological intervention for students experiencing AjD. Further objectives are to explore mechanisms for obtained changes. We expect that the online UP intervention will be an effective form of treatment, and we expect that obtained changes will be significantly greater than those from the two control conditions. We also predict that experiential avoidance, mindfulness skills, self-compassion, and cognitive fusion will mediate this effect.

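### One 80% power figure at d = 0.5 against an unnamed control does not describe the two contrasts that the trial aims to win at 2:2:1

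*Protocol article*

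**What the plan says.** The section Sample size calculation takes its effect size from earlier work: "Previous research on an online UP intervention and online interventions for AjD has revealed a between-group effect size at the level of" d = 0.5. It does not say whether those studies used passive or active controls. The calculation is then stated as "Assuming an alpha 0.05 with a power of 0.80" and a "post-treatment between-group effect size of *d* = 0.5 (iCBT-UP versus control), 190 participants in the three groups will be sufficient to detect assumed differences". Only one effect size is used for sizing, and no separate value is given for iPMR.

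Other sections set two comparisons:

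- Objectives, item 1, evaluates the intervention against the waiting list and against the active control.
- The iPMR section says "we want to evaluate whether changes obtained in iCBT-UP will be significantly higher, than those obtained in an active, well-researched comparator". It also says of the comparator that "PMR has been proven to reduce college students’ anxiety and stress and boost happiness".
- The Discussion states the hypothesis: "we expect that obtained changes will be significantly greater than those from the two control conditions".

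Randomization and blinding sets the allocation at 2:2:1, with the waiting list as the smallest arm.

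**The concern.** A reader of the sample size section will take 80% as the power of the trial's main comparisons. There are two of these, they have different arm sizes, and they need not share an effect size.

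On a common outcome scale, d against iPMR equals d against waiting minus the effect of iPMR over waiting. If 0.5 is used for both contrasts, the implied effect of iPMR over waiting is zero. That sits badly with the protocol's account of relaxation training as a proven technique in students. If 0.5 refers to the waiting list only, no power is stated for the active contrast.

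The active contrast carries the question of specific effect, and the Discussion counts the active control among the study's strengths. A non-significant result there, published beside a nominal 80% power, could be taken as evidence that the intervention is no better than relaxation when the trial may not have been able to tell.

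**Working it through.** **Inputs.** From Sample size calculation: alpha 0.05 (sidedness not stated, two-sided assumed here), power 0.80, d = 0.5, 190 analysed, 30% dropout, 247 recruited. From Randomization and blinding: 2:2:1.

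**1. Reproducing 190.** For a two-sided two-sample comparison with equal arms, n per arm = 2(1.96 + 0.84)²/d² = 2 × 7.85/0.25 ≈ 63. The noncentral t gives 64. Three equal arms give 189 or 192, which matches 190. Other routes fit worse: one-sided t-test 153; three-group ANOVA with f = 0.25, 158; alpha 0.025 per contrast, 234; a 2:1 contrast scaled up to 2:2:1, 240. The figure is therefore best explained as one pairwise contrast at equal allocation.

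**2. Arm sizes at 2:2:1.** 190 × 0.4 = 76 in iCBT-UP, 76 in iPMR, and 190 × 0.2 = 38 on the waiting list.

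**3. Power of each contrast at d = 0.5.** The noncentrality parameter is d × √(n₁n₂/(n₁ + n₂)).

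- Against iPMR: 0.5 × √(76 × 76/152) = 0.5 × 6.16 = 3.08. Power is 86.5%.
- Against the waiting list: 0.5 × √(76 × 38/114) = 0.5 × 5.03 = 2.52. Power is about 70%.

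**4. Smallest d with 80% power.** About 0.46 against iPMR (76 v 76) and about 0.56 against the waiting list (76 v 38).

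**5. Both contrasts significant.** The two test statistics share the iCBT-UP arm. Their correlation is √[(76/152) × (38/114)] = √(0.5 × 0.333) = 0.41. With d = 0.5 in both, a bivariate normal calculation gives about 65%. With equal arms the correlation is 0.5 and the result is about 69%.

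**6. If d against iPMR is smaller.** The document gives no effect of iPMR over waiting. Taking d = 0.5 as the effect over waiting and assuming that iPMR itself achieves 0.1 to 0.3:

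| d against iPMR | Power v iPMR (76 v 76) | Power for both (d = 0.5 v waiting list) |
|---|---|---|
| 0.5 | 86.5% | 65% |
| 0.4 | 69% | 54% |
| 0.3 | 45% | 38% |
| 0.25 | 33% | 29% |
| 0.2 | 23% | 21% |

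**7. Other analysed numbers, d = 0.5 in both contrasts.** With 247 less 30% (247 × 0.7 ≈ 173; arms 69:69:35), power is 83% against iPMR, about 66% against the waiting list and about 60% for both. If all 247 contributed full data (about 99:99:49), the figures are 94%, 81% and 79%. At d = 0.4 and 0.3 against iPMR, full retention gives 80% and about 55% for that contrast.

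**The case against.** Four objections have weight.

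- **The arithmetic at the stated assumption is sound for iPMR.** At d = 0.5 the iPMR contrast has 80% power with equal arms and 86.5% at 2:2:1. A reader might infer that the active comparison is underpowered as planned. That follows only if d = 0.5 is replaced by a smaller value. This objection stands.
- **The comparator behind d = 0.5 is not stated.** If the source studies used active controls, or if 0.5 is meant as a minimum for either contrast, iPMR may work and the effect over waiting may simply exceed 0.5. The benefits that the protocol reports for relaxation training concern anxiety, stress, depression and happiness, not adjustment disorder severity on the IADQ. So the document does not prove that d against iPMR is below 0.5. It makes an equal d doubtful and offers no support for one.
- **No rule requires both contrasts to be significant.** The Discussion states an expectation and the Objectives list comparisons. The 65% therefore describes the chance of seeing what the Discussion expects. It is not the power of a formal success criterion.
- **The planned model may gain power.** The analysis uses repeated measures, and change from baseline is among the planned comparisons. With an assumed baseline correlation of 0.5, d is in effect divided by √(1 − 0.25) = 0.866. Power at d = 0.3 against iPMR then rises from 45% to about 56%. A d of 0.5 behaves like 0.58, just above the 0.56 needed against the waiting list. But the sample size section claims no such gain and gives no correlation, so the stated 80% does not rest on it.

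What remains is that one power figure, for one unnamed contrast at equal allocation, stands behind two aims at unequal allocation.

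**Conclusion.** The point holds as a fault in the stated justification. At 190 analysed, 2:2:1, two-sided 0.05 and an unadjusted t-test, the single 80% describes neither contrast. At d = 0.5 it is too high for the waiting list (about 70%), too low for iPMR (86.5%), and well above the chance of significance against both (about 65%). If d against iPMR lies in the assumed range 0.4 to 0.2, power there is 69% to 23%.

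Three stronger readings are tempting, and the document does not support them:

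- That iPMR must be no better than waiting for the plan to work. This depends on what d = 0.5 was measured against, which is not given.
- That a null result against iPMR is the likely outcome. Power falls below one half only if d is below about 0.32, that is, if iPMR beats waiting by more than about 0.18 (with 0.5 taken as the effect over waiting).
- That the authors intend to read a null as equivalence. No section says so. The risk lies in how a reader would take it.

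**What to change.** In Sample size calculation, with no change in N:

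1. Name the comparator type behind d = 0.5.
2. Replace the single 80% statement with one line per contrast at the actual 2:2:1 arm sizes, giving power and the smallest d detectable with 80% power: about 70% at d = 0.5 and about 0.56 against the waiting list; 86.5% and about 0.46 against iPMR.
3. For iPMR, add the power at d = 0.4, 0.3 and 0.2 (69%, 45%, 23%), marked as an assumed range.
4. State the lower power for both contrasts together (about 65% with d = 0.5 in each).
5. Say that the iPMR contrast will be reported as an estimate with a 95% CI, and that non-significance will not be read as equivalence.

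The 80% must not simply be reassigned to the waiting-list contrast. At 76 v 38 that contrast has about 70% power at d = 0.5, and about 66% at 69 v 35. If the authors wish to take credit for baseline adjustment, they should state the assumed correlation and recompute both lines.

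The cost is some rewording and a less favourable stated power. No extra participants are needed.

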### Objectives

The main objective of the planned research is to evaluate the effectiveness of an online UP intervention among students experiencing AjD.

More specific objectives are as follows: (1) evaluate the effectiveness of the intervention relative to waiting-list and active control groups according to self-reported measures; (2) investigate the effectiveness of the intervention in the daily lives of participants; (3) assess the effectiveness of the intervention in the cognitive functioning of students; (4) conduct an examination of predictors and mediators of treatment response; (5) compare the impact of both treatment approaches, with different putative mechanisms of action, on outcome measures; and finally (6) evaluate the maintenance of AjD alleviation at 1-month follow-up.

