### Randomization and blinding

Subjects who meet the inclusion criteria will be randomized to one of two active groups or the waiting-list group using a 2:2:1 allocation ratio. The participants will be randomly allocated using a computerized block randomization, using block sizes of 6. Random allocation will be performed using an algorithm developed by a computer scientist and executed independently of the research team by an independent program [49]. The main researcher will then reveal the concealed allocation and inform participants of their placement into one of three groups. Randomization will be stratified based on the score of the initial AjD questionnaire assessment (the IADQ; see description below). The principal investigator responsible for determining study eligibility will be blinded to the randomization sequence. The researchers and psychotherapists leading the study and contacting participants cannot be blinded to allocation for practical reasons; however, those conducting the MINI evaluation will be blind to the condition allocation during the assessment.

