#### Questionnaires

##### Primary outcome measures

The International Adjustment Disorder Questionnaire (IADQ) [59] is a 19-item questionnaire used to assess AjD related to ICD-11 criteria [13]. The IADQ consists of nine item stressor list, three items that assess preoccupation with the stressor, three items that consider symptoms of failure to adapt, three items that assess functional impairment, and one item that assess duration of symptoms. The primary endpoint for this outcome is immediately post intervention. Then, we will assess it after a one-month follow-up to evaluate the stability of the obtained changes. We will compare post-test scores between three conditions as well as change from baseline measurement.

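### The sample size powers iCBT-UP against one unnamed control, but the trial has two, and the stated 0.80 power fails for a two-sided waiting-list contrast and for superiority to both

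*Protocol article*

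**What the plan says.** The primary outcome and its time point are fixed: the IADQ, immediately after the intervention (Primary outcome measures). The comparison is described in several places, in different ways.

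- **Sample size calculation:** "Assuming an alpha 0.05 with a power of 0.80" and an effect of d = 0.5, the section sets out its contrast and conclusion as "iCBT-UP versus control), 190 participants in the three groups will be sufficient to detect assumed differences". Control is singular and is not identified.
- **Study design:** iPMR is labelled the active control group and WLC the waiting-list control group, so both arms fit the word.
- **Randomization and blinding:** participants are "randomized to one of two active groups or the waiting-list group using a 2:2:1 allocation ratio", so the two candidate controls differ in size by a factor of two.
- **Objectives, item 1:** "evaluate the effectiveness of the intervention relative to waiting-list and active control groups according to self-reported measures". Both controls appear, unranked.
- **Primary outcome measures:** "We will compare post-test scores between three conditions". No contrast is singled out.
- **Discussion:** "we expect that obtained changes will be significantly greater than those from the two control conditions". This is an expectation, not a decision rule.

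The intervention sections give the controls different purposes. iPMR tests whether iCBT-UP does better than an established active comparator. WLC separates the effect of treatment from the passage of time.

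**The concern.** The two contrasts answer different questions and, under 2:2:1 allocation, have different precision. A power statement for an unnamed control therefore cannot be checked, and the one figure given cannot be true of every claim the protocol intends to make.

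Two things are at stake. First, the stated 0.80 may not apply to the comparison that ends up carrying the conclusion. Second, if the result is significant against one control and not the other, the document does not say whether the trial succeeded, so that reading would be settled after the data are seen.

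**Working it through.** **Inputs from the protocol.** Alpha 0.05, power 0.80, d = 0.5, N = 190 (Sample size calculation); allocation 2:2:1 (Randomization and blinding). Arms at N = 190: iCBT-UP 190 × 2/5 = 76, iPMR 76, WLC 190 × 1/5 = 38.

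**Assumptions.** Two-sided testing, since sidedness is not stated; the one-sided result is also shown. A simple comparison of post-treatment means with SD = 1, without the gain that baseline adjustment might bring. A true d = 0.5 against each control unless stated otherwise, because the protocol gives no separate effect against iPMR.

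**1. Where 190 could come from.** Two incompatible routes lead there.
- One-sided t-test against WLC at 2:1: 76 + 38, plus 76 for iPMR = 190 exactly.
- Two-sided test with equal arms: 3 × 63 = 189 (normal approximation) or 3 × 64 = 192 (t-test). This ignores the 2:2:1 ratio.

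Under 2:2:1 and two-sided 0.05, neither contrast gives 190. iCBT-UP against iPMR needs 64 + 64 + 32 = 160; iCBT-UP against WLC needs 96 + 96 + 48 = 240. The total therefore does not reveal the intended control.

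**2. Power of each contrast at 76:76:38.** Noncentrality = d × √(n₁n₂/(n₁+n₂)), with power from the noncentral t distribution.

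| Contrast | Noncentrality | Power, two-sided 0.05 |
|---|---|---|
| iCBT-UP vs iPMR | 0.5 × √(76×76/152) = 3.08 | 86% |
| iCBT-UP vs WLC | 0.5 × √(76×38/114) = 2.52 | 70% |

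Against WLC, a one-sided 0.05 test has 80.4% power.

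**3. Both contrasts together.** They share the iCBT-UP arm, so their correlation is (1/76)/√[(1/76+1/76)(1/76+1/38)] = 1/√6 = 0.41. The bivariate normal approximation has marginal powers of 86.9% and 71.1%, slightly above the t values.
- Both significant: 65%.
- Exactly one significant: 86.9% + 71.1% − 2 × 65.1% = 27.8%, about 28%.

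**4. Type I error if either contrast sufficed, unadjusted.** With no true differences, P(|z₁| > 1.96 or |z₂| > 1.96) at correlation 0.41 is 9.3% (9.75% if independent).

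**5. Sensitivity to the iPMR effect.** Keep d = 0.5 against WLC and assume a smaller d against iPMR.

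| Assumed d vs iPMR | Both significant | Significant vs WLC only |
|---|---|---|
| 0.3 | 38% | 33% |
| 0.2 | 20–21% | 51% |
| 0 | 2% | 69% |

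**The case against.** **An unseen analysis plan may hold the testing rules.** Multiplicity procedures are often left to that document, and their absence here is not the point. What stands is that this document states a power figure for a contrast it does not identify, and its other sections describe two contrasts and a claim about both.

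**The protocol already points to a both-controls criterion.** iCBT-UP is the index arm throughout, each control has a stated purpose, and the Discussion expects superiority over both. A formal rule requiring both would not inflate the type I error. This is a fair reading, but the text states an expectation only, and under that rule the 0.80 does not apply.

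**The shortfall against WLC comes from N and allocation.** Largely true: the 70% would remain after the contrast is named. Naming it is what makes the shortfall visible.

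A reader might also infer stronger claims that the document does not support:
- *That every contrast will be tested at the full 0.05.* The 0.05 appears only as a sample-size input.
- *That any significant contrast counts as success.* No such rule is adopted, so 9.3% is conditional on it.
- *That three pairwise tests inflate the error to about 12%.* That count includes iPMR against WLC, which no objective names as a test of iCBT-UP; objective 5 compares the two treatments, which is already one of the two contrasts.
- *That the contrasts can give opposite conclusions.* A gain over WLC without one over iPMR is coherent: better than time alone, not shown better than relaxation. With a true d of 0 against iPMR it is the correct result. The rates in step 5 also rest on iPMR effects the protocol does not give.

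**Conclusion.** The point holds. The sample size section powers one contrast against an unidentified control, and no section states which contrast or combination decides the trial. At N = 190, 2:2:1, d = 0.5 and two-sided 0.05, the stated 0.80 is exceeded against iPMR (86%), is not met against WLC (70%), and is not met for superiority to both (about 65%). It holds against WLC only if the test is one-sided.

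The open success rule matters because split results are not rare: about 28% even when the true effect is 0.5 against both controls. The 9.3% family-wise error describes what would follow if either contrast were accepted unadjusted; it is not a property of the plan as written.

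The power figures rest on d = 0.5 for each contrast, 190 analysed participants in exact 2:2:1 proportion, and an unadjusted comparison of post-treatment means. Correlation with baseline in the planned hierarchical model could raise power, but the protocol gives no value for it.

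**What to change.** In Primary outcome measures and Sample size calculation:

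1. Name two confirmatory contrasts on the IADQ at t2: iCBT-UP against WLC, and iCBT-UP against iPMR.
2. State how they are tested: a fixed sequence given in advance (for example WLC first, then iPMR only if the first is significant), or Holm over the two if no order is wanted.
3. Label iPMR against WLC and all t3 contrasts secondary.
4. State that superiority to both controls is claimed only if both contrasts are significant.
5. Replace the unnamed control with the named contrasts, state sidedness, and give the power for each contrast and for both jointly.

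**Cost.** These are wording changes, with no extra enrolment or data required. The reported power becomes less favourable: about 70% for the WLC step at N = 190, two-sided. Restoring 0.80 for that step would take 240 analysed participants at 2:2:1, so leaving N unchanged means accepting the lower figure openly. Under a fixed sequence, a failed first step bars a confirmatory claim on the second; Holm avoids that but tests the smaller p-value at 0.025.

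### The 190 participants said to give 80% power do not fit the 2:2:1 allocation under a two-sided test: the unadjusted iCBT-UP versus waiting-list contrast then has about 70% power

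*Protocol article*

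**What the plan says.** The protocol's Sample size calculation section gives the error rate and power as "Assuming an alpha 0.05 with a power of 0.80" and the effect as a "post-treatment between-group effect size of *d* = 0.5 (iCBT-UP versus control"). From these it concludes that "190 participants in the three groups will be sufficient to detect assumed differences". The software is named as G*Power. The section does not give the test family, the number of sides, the allocation ratio or the control to which d = 0.5 refers.

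The ratio is fixed under Randomization and blinding, where participants are "randomized to one of two active groups or the waiting-list group using a 2:2:1 allocation ratio". The waiting list is therefore the smallest arm.

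Both controls matter to the aims. The first specific objective is to "evaluate the effectiveness of the intervention relative to waiting-list and active control groups according to self-reported measures", and the Discussion says "we expect that obtained changes will be significantly greater than those from the two control conditions". The Waiting List Control section explains that this arm is there to separate the effect of the programme from the passage of time.

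**The concern.** Power for a two-group contrast depends on the sizes of the two groups compared, not on the trial total. A total of 190 at 2:2:1 leaves only 38 in the waiting list, and the sample size section does not show that this was taken into account. If it was not, the stated 80% is too high for the comparison that separates the programme from spontaneous recovery. The chance of missing the planned effect in an unadjusted two-sided comparison would be about 30% instead of 20%. A non-significant result against the waiting list could then be read as stronger evidence against the programme than the design can supply.

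**Working it through.** **Inputs.** From Sample size calculation: alpha 0.05, power 0.80, d = 0.5, total 190. From Randomization and blinding: ratio 2:2:1. Sidedness is not stated, so both cases are computed.

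**Arm sizes.** 190 / 5 = 38, so the arms are 76 iCBT-UP, 76 iPMR and 38 waiting list.

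**Reproducing 190.** By the normal approximation, the smaller group (n₂) in a comparison with ratio k:1 needs n₂ = (1 + 1/k)(z_alpha + z_beta)² / d². The t-test figures use the noncentral t distribution.

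- *Two-sided, equal arms (k = 1):* 2 × (1.960 + 0.842)² / 0.25 = 62.8, so 63 per arm and 3 × 63 = 189. The t test needs 63.8, so 64 per arm and 192. At 190 / 3 = 63.3 per arm, t-test power is 0.797.
- *One-sided, 2:2:1 (k = 2):* 1.5 × (1.645 + 0.842)² / 0.25 = 37.1, so 38 in the waiting list. The t test needs 37.6, also 38. The total is 5 × 38 = 190, with power 0.804.
- *Two-sided, 2:2:1 (k = 2):* 1.5 × (1.960 + 0.842)² / 0.25 = 47.1, so 48. The t test needs 47.7, also 48. The total is 5 × 48 = 240.
- *One-sided, equal arms:* the t test needs 51 per arm, total 153.
- *One-way ANOVA with three groups, f = 0.25:* about 158.

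The first two routes land on or next to 190. The other three do not.

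**Power of 190 as allocated, two-sided 0.05, d = 0.5.**

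- *iCBT-UP versus waiting list:* noncentrality = 0.5 × √(76 × 38 / 114) = 2.517. Power is 0.704 by the t test and 0.711 by the normal approximation.
- *iCBT-UP versus iPMR:* noncentrality = 0.5 × √(76 × 76 / 152) = 3.082. Power is 0.865 by the t test, provided d = 0.5 also holds against this active comparator.

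**Two-sided 80% against the waiting list at 2:2:1.** 96 versus 48 gives 0.802, which means 96 + 96 + 48 = 240 analysed.

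**Effect of baseline adjustment.** The protocol gives no pre-post correlation r, so these values are assumptions. Adjustment for baseline raises the effective d to 0.5 / √(1 − r²). For 76 versus 38, two-sided:

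| r | effective d | power |
|---|---|---|
| 0 | 0.500 | 0.70 |
| 0.3 | 0.524 | 0.74 |
| 0.4 | 0.546 | 0.78 |
| 0.45 | 0.560 | 0.80 |
| 0.5 | 0.577 | 0.82 |

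**The case against.** **A one-sided test may have been meant.** If so, 76 versus 38 has 0.804 power and 190 is exactly right. This stands as a possibility, and the Discussion's expectation is directional. An expected direction does not declare a one-sided test, however, and none is declared anywhere.

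**A reader might infer the opposite: that the exact match proves a one-sided calculation.** The protocol does not support that either. A two-sided calculation with three equal arms gives 189 to 192, and 0.797 at 63.3 per arm rounds to the stated 0.80. The block size of 6 in Randomization and blinding divides evenly among three equal arms but is not a multiple of 5, which also fits equal arms, though it proves nothing. The 95% intervals in Data analysis do not settle the matter, because they are specified for the bootstrap mediation effects and not for the primary contrast.

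**The control meant may be iPMR.** Power is then 0.86 and there is no shortfall. The text does not say which control is meant, and the waiting-list comparison is a stated objective.

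**The planned analysis is not an unadjusted t test.** This has force. Data analysis specifies hierarchical linear modelling, and the primary outcome section includes change from baseline. At r of about 0.45 or more the waiting-list contrast would reach 0.80. But the calculation is built on a post-treatment between-group d and states no correlation, so the protocol does not claim this gain.

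**The larger recruitment target covers the gap.** With all 247 analysed, two-sided power against the waiting list would be 0.81. The 247 is there to absorb about 30% dropout, however. On that assumption 247 × 0.7 = 173 remain, and power is 0.66.

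**Conclusion.** The statement is wrong as written under the conventional two-sided reading. At 2:2:1, 190 analysed participants give about 70% power for the unadjusted iCBT-UP versus waiting-list contrast, 10 points below the stated 80%, and 80% would take 240. Either the calculation ignored the trial's allocation ratio or it used a one-sided test that is not declared; the protocol does not show which.

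The conclusion rests on a two-sided 0.05 test, d = 0.5, exact 2:2:1 arms and no baseline adjustment. It does not extend to the iPMR contrast, which has about 86% at the same d.

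A reader might infer that the trial as a whole is underpowered, or that it should be judged on the probability of winning both contrasts. The protocol does not support that. It powers a single pairwise effect, sets no rule that both comparisons must succeed, and gives no smaller effect size for the active comparator. A 30% miss rate is likewise not established for the planned model, whose power depends on a correlation that the protocol does not give.

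**What to change.** Revise the Sample size calculation paragraph so that it agrees with the allocation ratio:

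1. State whether the test is one- or two-sided, which control d = 0.5 refers to, and whether 190 was derived with equal arms. If a one-sided test was meant, say so and justify it.
2. Give the arm sizes (76:76:38 for 190 analysed) and the two-sided power of each contrast: about 0.70 against the waiting list, and about 0.86 against iPMR if d = 0.5 is assumed there too.
3. If the plan relies on a baseline-adjusted analysis, state the assumed pre-post correlation, its basis and the resulting power for 76 versus 38, with a range such as 0.74 at r = 0.3, 0.80 at r = 0.45 and 0.82 at r = 0.5.

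The cost is rewording one paragraph. No extra participants are needed to report the power correctly. The downside is a less favourable stated power for the waiting-list contrast unless a baseline correlation of about 0.45 or more can be justified.
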